## Discussion

Most psychosocial interventions are targeted at immigrant children generally or to those who suffer from PTSD or other symptoms. There is a lack of universal interventions embedded in classrooms with both immigrant and native peers together [9, 19, 38]. Professionals recommend combining both preventive universal psychosocial elements and targeted clinical therapies, tailored according to the needs of immigrant children [18, 20, 32]. The number of immigrant children with an increased risk for mental health problems is growing. To understand the extended effect of school-based interventions, we need to broaden the research to include also information about child-, school-, and family-related factors [32, 38]. Similarly, the knowledge of what works for whom, why, and where would be of great importance when tailoring effective treatment for immigrant children. In trauma research, the relevant questions are about the factors and processes (or mechanisms) that explain (statistically mediate) the impact of war trauma on children’s and adolescents’ mental health and who are most vulnerable to negative trauma impacts, and why [75]. Analogously, in intervention studies, it is critical to know what explains the potential change and to whom interventions work and why.

As a limitation to the study, unfortunately, the recruitment did not reach the needed number of clusters for adequate power of 80%. The problems in the recruitment may have been because many schools had other ongoing interventions or had just participated in similar training. Some schools with a long history of teaching immigrant students doubted the intervention could provide them with any new tools. In more rural schools near asylum centers, the number of immigrant students had decreased rapidly after the great influx in 2015, and the intervention was thus not seen as necessary anymore. The low power will limit our chances of finding statistically significant effects on a school level.

The COVID-19 outbreak did not affect the training of the facilitators for the INSETT, TRT, or PIER interventions in Finland, as they were conducted in September 2019 to January 2020. However, the implementation of the TRT failed in the five schools that had planned the group sessions in spring 2020. The baseline assessment was conducted in classrooms as planned (August to September 2019), but due to the COVID-19 school closure, the timing of the 6- to 12-month assessments was delayed. Students were individually contacted by text messages, and they responded online, which was not as effective as conducting the data collection in classrooms.

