Concerning INSETT, we hypothesize that participation of teachers increases their multi-cultural awareness, sense of self-efficacy, and work engagement and decreases their work stress, which in turn are associated with the decreased internalizing and externalizing symptoms and increased prosocial behavior and resilience among the adolescents.We hypothesize that adolescents’ participation in PIER intervention is associated with their increased social support, feeling of belongingness, number of inter-ethnic friendships, and satisfaction on friendships, which in turn is associated with decreased internalizing and externalizing symptoms and increased prosocial behavior and resilience.We hypothesize that adolescents’ participation in TRT intervention is associated with decreased PTSD symptoms of intrusion and avoidance, which in turn is associated with decreased internalizing and externalizing symptoms and increased prosocial behavior and resilience.How do parent- and adolescent-related factors moderate the effectiveness of the two arms of school-based psychosocial interventions of INSET+TRT and PIER?
We hypothesize that good parental mental health and parents’ high sense of competence and confidence in parenting are associated with a statistically significant positive intervention-induced change in adolescents’ mental health (i.e., decreased internalizing and externalizing symptoms and increased prosocial behavior and resilience).We hypothesize that adolescents who report the low frequency of daily stressors and low perceived discrimination show more statistically significant positive intervention-induced change in their mental health (i.e., decreased internalizing and externalizing symptoms and increased prosocial behavior and resilience).

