## Study setting and participants

Power calculations were conducted before the data collection started. With alpha set at 0.05, power at 0.80, and rho = 0.05 (the intra-cluster correlation), a sample size of at least 40 clusters (i.e., schools) with 25 youths each was identified as necessary. Therefore, 500 youths per study arm (i.e., intervention or wait list control) were needed, resulting in 1500 total participants. To account for an expected drop-out rate of 20%, 1800 youths would have been recruited in total. To facilitate the recruitment of so many participants, recruitment was split between the Finnish study team and our team partners in Sweden.

The interventions were implemented in lower secondary schools with grades 7–9 and/or introduction classes for newcomer youth. We focused on immigrant youth who have resided in Finland for less than 6 years. Figure 1 presents the flowchart of the recruitment. Seventeen schools expressed their interest in participating in the study, but after allocation, one school dropped out. According to the randomization, eight schools were allocated into the INSETT+TRT intervention, three schools were allocated into PIER, and five schools served as waiting list controls. Also, Fig. 1 reports the numbers of students, teachers, and parents who answered the survey in the first round of data collection.

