## Recruitment and sampling

The recruitment of schools was based on three aspects. First, voluntariness, i.e., their (headmasters and teachers’) self-defined need for intervention, knowledge, and training on psychosocial skills while teaching refugee and immigrant adolescent students. For that purpose, the first recruitment was through advertisement in the national teachers’ magazine (Opettaja) and email lists to school administration in every municipality in Finland. Second, the recruited and voluntary schools should have a considerable share of refugee and immigrant background pupils in secondary school classes estimated as 30–50% in each class. Third, the schools accepted the possibility of serving as a waiting list school until the next school year when they would be provided the INSETT intervention in electronic form. The first wave of recruitment was complemented with about 100 phone calls to headmasters of schools residing in the metropolitan or otherwise immigrant-dense areas of larger cities in Finland. In the second wave of recruitment, phone calls and e-mail communications were established to invite schools close to asylum centers in numerous towns and municipalities in Finland. However, most extra work to reach schools near asylum centers and the metropolitan area was not successful as schools informed that they already had several general interventions (such as anti-bullying whole-school programs) or trauma and refugee-focused programs (such as cultural coaching programs). As a result of the two waves of recruitment, 16 schools agreed to participate in the Refugees Well School study.

Table 1 presents the study period for implementing interventions, collecting data (T1, T2, T3), and specific measures for adolescents, teachers, and parents. Baseline data was collected before the interventions, INSETT+TRT and PIER interventions were implemented between September 2019 and January 2020, post-intervention data collection took place around February 2020, and the follow-up data will be collected in August 2020. INSETT will be provided to waiting list control schools in October 2020.

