## Analytic strategy

Due to the sampling procedure, our data will be clustered in two levels: pupils are nested in 134 classes, and classes in 16 schools. The data contains variables from individual, class, and school levels, and the interventions are given at the school level. All the indicators of outcome variables are measured at all three time points at the individual level. T1 was collected before the intervention, T2 20 weeks after the intervention started, and T3 as a follow-up 52 weeks after the beginning of the intervention. We expect the intervention to change the levels in outcomes from T1 to T2, and the new levels to remain the same through T3 follow-up.

The structure of the data requires the use of structural equation (SEM) methods combining longitudinal, multi-level, path analytic models with confirmatory factor analysis. The psychometric properties of the outcome variables, including measurement invariance between time points T1, T2, and T3, are tested before constructing summary scales using the most reliable items. The scales are then specified as manifest variables in the models. Alternatively, latent constructs are used, depending on the complexity of the final model specifications. The core model in all our analyses will be a version of latent growth curve model [72, 73], that is also known as intervention model [74] due to the coding of the fixed parameters in the model, which are responsible for the shape of the constant growth trajectories at the individual level (the 1’s in Fig. 2). The latent growth parameters will be estimated with the Mplus 8.0 software using a robust maximum likelihood estimator (MLR), which allows non-normal continuous indicators to be reliably analyzed. Additionally, MLR is a full-information estimator allowing the use of missing data without any separate imputations. The validity of the MAR assumption is scrutinized, and if needed, auxiliary variables predicting missingness will be added into the models. Demographic and baseline characteristics will be summarized using means and standard deviations for quantitative variables and percentages for categorical variables.

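### The protocol dates delivery of INSETT+TRT to before T2 but also reports that TRT failed in five schools, so neither the arm effect nor the CRIES-8 mediation path can be read as an effect of delivered TRT

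*Protocol article*

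**What the plan says.** **Delivery dates.** Recruitment and sampling in the protocol article states that "INSETT+TRT and PIER interventions were implemented between September 2019 and January 2020, post-intervention data collection took place around February 2020". Analytic strategy places the surveys relative to the start of intervention: "T2 20 weeks after the intervention started, and T3 as a follow-up 52 weeks after the beginning of the intervention".

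**What happened to TRT.** The COVID-19 paragraph of the Discussion gives September 2019 to January 2020 as the window for facilitator training, which it says was untouched by the pandemic. It then says that "the implementation of the TRT failed in the five schools that had planned the group sessions in spring 2020".

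**Size of the arm.** Under Study setting and participants, "eight schools were allocated into the INSETT+TRT intervention". Three schools went to PIER and five to the waiting list. No other arm includes TRT.

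**What is to be estimated.** Measures makes T1 to T2 the primary interval. Under Objectives, one mediation hypothesis is specific to TRT: adolescents' "participation in TRT intervention is associated with decreased PTSD symptoms of intrusion and avoidance", which is in turn linked to the primary outcomes. The explanations to Fig. 2 code a single status for INSETT+TRT and list CRIES-8 as the mediator belonging to TRT. Analytic strategy defines the direct and indirect effects from an indicator of intervention or control membership. It also expects outcome levels to change by T2 and then hold to T3.

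**The concern.** The two accounts of delivery do not agree. One has INSETT+TRT completed before the post-intervention survey. The other has TRT sessions in five schools planned for spring 2020, outside that window, and not successfully carried out. Nothing in the article carries this into the hypotheses, the definition of the contrast or the model, although the failure is reported in a protocol dated 1 July 2020.

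Two readings of the results are at risk. A null arm effect could be taken as evidence against the combined targeted programme when most of its schools may have had INSETT without TRT. A path through CRIES-8 could be taken as TRT working by reducing trauma symptoms. INSETT is itself meant to support the mental health of trauma-affected students (The interventions), so it could produce such a path with no TRT at all.

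**Working it through.** **1. The T2 date.** Start of intervention: September 2019 (Recruitment and sampling). T2: 20 weeks later (Analytic strategy).
- 1 September 2019 + 20 weeks = 19 January 2020.
- 30 September 2019 + 20 weeks = 17 February 2020.

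This reproduces the stated T2 of around February 2020. The survey timetable is coherent, and TRT delivery is what does not fit it.

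**2. The two accounts side by side.**

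| Item | Recruitment and sampling | Discussion |
|---|---|---|
| September 2019 to January 2020 | Both active interventions implemented | Window given for facilitator training |
| TRT group sessions | Covered by the same window | Planned for spring 2020 in five schools, and failed there |

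For those five schools the first account cannot be right about TRT.

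**3. Share of the arm affected.** Allocation: 8 + 3 + 5 = 16 schools, as stated. TRT belongs only to the arm of eight, so the five schools are taken to be among them.
- Failed: 5/8 = 62.5%.
- Could have delivered as planned: at most (8 − 5)/8 = 3/8 = 37.5%.

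**4. What the arm contrast contains.** Let k be the number of schools that delivered TRT and D the school-average effect specific to TRT. Assume schools of equal size and no TRT effect where TRT failed. The arm contrast is then

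INSETT effect + (k/8) × D, with k at most 3.

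| k | Share of D in the contrast |
|---|---|
| 0 | 0 |
| 1 | 0.125 |
| 2 | 0.25 |
| 3 | 0.375 |

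The ratio needs no assumed value of D. The article states no effect size, so none is used here.

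**5. The mediation path.** The hypothesis speaks of participation in TRT. The exposure in the stated model is membership of the arm. With k at most 3, the two differ in at least five of the eight schools, and the indirect effect through CRIES-8 mixes any INSETT effect on trauma symptoms with whatever TRT was given.

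**The case against.** Several points on the other side are fair.

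- **Order relative to T2.** A reader might infer that the failed sessions were due after T2. The article does not say so. It gives spring 2020 for the sessions and around February 2020 for T2. The Discussion adds that the 6- to 12-month assessments were delayed, and Objectives calls T2 the 6-month follow-up. The order cannot be settled, but the point does not depend on it: the sessions lay outside the stated window and failed.
- **Number of schools.** That the five belong to the eight is implied, not stated. Nor does the article say that the other three delivered TRT, so a count of exactly three would be unsupported. Three is an upper bound. Failure might also include partial delivery.
- **What is tested.** A reader might infer that a separate TRT main effect is planned. It is not: the main comparison is of the combined arm with control, and analysis by allocation is right under non-delivery. Only the CRIES-8 hypothesis is specific to TRT.
- **Model wording.** The membership indicator belongs to a core model of which each analysis uses a version, so a full analysis plan might code TRT delivery. That is possible, but it would not correct the stated delivery dates or the labelling in Fig. 2.
- **Disclosure.** The failure is reported openly, close to the power limitation. What is lacking is any consequence for the analysis.

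These points limit how firmly the counts and timing can be put. They do not remove the contradiction or the mismatch between the TRT label and the exposure.

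**Conclusion.** The point holds. The sections on delivery contradict each other and must be reconciled. At most 3 of 8 schools (37.5%) in the INSETT+TRT arm could have delivered TRT as planned, on the assumption that the five failed schools are all in that arm. With equal-sized schools and no TRT effect where it failed, the arm contrast holds at most 3/8 of any TRT-specific effect.

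The as-randomised comparison is not invalid. It estimates the effect of being allocated to INSETT+TRT under the delivery that occurred. It does not estimate the efficacy of TRT or of the fully delivered package, and the CRIES-8 path is not evidence of a TRT mechanism.

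**What to change.** 1. Reconcile Recruitment and sampling with the Discussion, and state for each INSETT+TRT school whether TRT was delivered in full, in part or not at all.
2. Keep the as-randomised comparison. Define it as the effect of allocation to INSETT+TRT with TRT delivered in at most 3 of 8 schools, replacing the bound by the confirmed number. Draw no conclusion from it about the efficacy of TRT or of the complete package.
3. Report results separately for schools that did and did not deliver TRT, labelled as a non-randomised sensitivity analysis.
4. Keep allocation as the exposure in the CRIES-8 mediation model, call the analysis exploratory, and do not interpret the path as specific to TRT.
5. Make any analysis by actual TRT participation supplementary, and run it only if attendance was recorded, which the article does not say. Adjust it for baseline CRIES-8 and flag it as confounded: Trial design says TRT is aimed at recently arrived refugee youth, so participation is likely to be related to trauma symptoms at baseline. It should not replace allocation, because that would give up the randomised exposure.

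The cost is revised wording, one small extra analysis and a weaker claim about TRT.

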## Dissemination

The results of this trial will be submitted for publication during 2021–2023, and publications will be made open access. The authorship of future trial publications will be determined by the research group, and other members of the H2020 consortium will be invited accordingly. Professional language editing will be used. The INSETT and PIER Finnish-language intervention manuals will be prepared open-access to schools. The data sets generated during the study will not be made open access but can be requested from the first author and according to the ethical approval.

Horizon 2020 did not influence the research design, conduct, or analysis. Also, the academic publications in national and international journals will not be influenced by the funder. However, the reports and deliverables requested by the EU will be offered as requested.

## Trial status

This is the first version of the study protocol (dated 1 July 2020). Recruitment began in January 2019 and was completed in August 2019. The data collection ended in September 2020, and the protocol was submitted before that.

## Data Availability

RWS consortium will manage and store the research data and will have a common data management plan available online.

## Abbreviations

BBI: Bergen Burnout Inventory
CBT: Cognitive-behavioral therapy
GHQ-12: General Health Questionnaire
CRIES-8: Children’s Impact of Events Scale
CYRM-12: Child and Youth Resilience Measure
DSSYR: Daily Stressors Questionnaire
ESSI: Enriched Social Support Instrument
INSETT: In-Service Teacher Training
MaaP: Me as a Parent
MAR: Missing at random
MLR: Robust maximum likelihood
MSPSS: Multidimensional Scale of Perceived Social Support
PEDQ-CV: Perceived Ethnic Discrimination Questionnaire Community Version
PIER: Peer Integration and Enhancement Resources
PSSM: Psychological sense of school membership among adolescents
PTSD: Posttraumatic stress disorder
RCT: Randomized control trial
SDQ: Strengths and Difficulties Questionnaire
SEM: Structural equation modeling
SISI: Single-Item Stress Index
TF-CBT: Cognitive-behavioral treatment with trauma-focus
TSES: Teachers’ Sense of Efficacy Scale
TMAS: Teacher Multicultural Attitude Scale
TRT: Teaching Recovery Techniques
UWES: Utrecht Work Engagement Scale
